## Abstract

**Introduction:**

Many people ageing with HIV are also living with multiple comorbidities and geriatric syndromes including frailty and cognitive deterioration. These complex needs can be challenging to meet within existing HIV care services. This study investigates the acceptability and feasibility of screening for frailty and of using a comprehensive geriatric assessment approach, delivered via the Silver Clinic, to support people living with HIV affected by frailty.

**Methods and analysis:**

Mixed-methods, parallel-group, randomised, controlled feasibility trial aiming to recruit 84 people living with HIV≥50, identified as frail. Participants will be recruited from the HIV unit at the Royal Sussex County Hospital, University Hospitals Sussex NHS Foundation Trust, Brighton, UK. Participants will be randomised 1:1 to receive usual HIV care or the Silver Clinic intervention, which uses a comprehensive geriatric assessment approach. Psychosocial, physical and service use outcomes will be measured at baseline, 26 weeks and 52 weeks. Qualitative interviews will be conducted with a subset of participants from both arms. Primary outcome measures include recruitment and retention rates and completion of clinical outcome measures. These will be used in conjunction with a priori progression criteria and the qualitative data (acceptability of trial procedures and intervention) to determine the feasibility and design of a definitive trial.

**Ethics and dissemination:**

This study has been approved by East Midlands—Leicester Central Research Ethics Committee (reference 21/EM/0200). All participants will receive written information about the study and be required to provide informed consent. Results will be disseminated via peer-reviewed journals, conferences and community engagement.

**Trial registration number:**

ISRCTN14646435.

STRENGTHS AND LIMITATIONS OF THIS STUDYThis study will evaluate the feasibility of screening for frailty and applying a comprehensive geriatric assessment, delivered via outpatient HIV services.The inclusion of qualitative methods will provide an understanding of how to optimise the intervention.The comprehensive set of outcome measures will capture information about physical and cognitive impairment, overall well-being, social interaction and healthcare utilisation.A feasibility randomised controlled trial design allows for testing the acceptability and feasibility of a full-scale trial and refining of the intervention.It is not possible to blind participants to their trial arm or the healthcare professionals delivering the intervention.

## Introduction

Of the people accessing HIV services in the UK, 39% are now aged 50 and over.^1 2^ People living with HIV (PLWH) over 50 appear to experience a disproportionate amount of comorbidities in comparison to their HIV negative counterparts, particularly in regard to geriatric syndromes, such as frailty and cognitive deterioration, which they experience at younger ages.^3 4^ Studies including a younger cohort of PLWH aged 50–64 demonstrate a frailty prevalence comparable to that of HIV negative cohorts aged 65 and older.^5^ As such, PLWH may not yet have reached the current UK recommended ages for frailty identification advocated in primary, secondary and community care settings.^6 7^ This coupled with the potential limited access to geriatric and other frailty services based on age alone, runs the risk of delayed identification of frailty and identification at a more severe stage where interventions may be less effective, resulting in greater health and social care costs.^8^

Current models of HIV care are not addressing the needs of people with HIV, with 47% of healthcare and 62% of social care needs not being met.^9^ Moreover, current care models may disadvantage older people living with HIV (OPWH) with, or at risk of, frailty as they can bounce between specialist HIV services and primary care. HIV specialist healthcare professionals (HCPs) often lack the awareness and experience to identify and manage frailty, and many general practitioners (GPs) lack knowledge and confidence around HIV.^10 11^ Use of multiple services can be especially challenging for some OPWH who avoid seeking care in non-HIV services because of perceived or experienced stigma and discrimination,^12^ which is often highlighted in community engagement work.^13–15^

To address this problem, the British HIV Association standards of Care for PLWH state that involvement of a geriatrician with HIV knowledge will strengthen service provision, though how to achieve this is unknown.^16^ The European AIDS Clinical Society guidelines recommend screening for frailty in people with HIV^17^ and while tools to identify patients at risk of frailty using scoring methods are increasingly used internationally^18^ and have recently been integrated into UK primary care, it is unknown if screening for frailty among OPWH is acceptable, feasible and useful as part of HIV services, particularly for those who are not chronologically elderly. Evidence-based models of care for OPWH at risk of frailty are needed to inform services on how to best to provide care for patients as described by The King’s Fund: The future of HIV services in England, shaping the response to changing needs document.^19^ Two national surveys led by our team^20 21^ and work by community organisations^4^ underscore the need for evidence-based guidance on how to best to provide care for OPWH.

The comprehensive geriatric assessment (CGA) is a multidimensional, interdisciplinary diagnostic process used to determine the medical, psychosocial and functional capabilities of older adults. The CGA has been studied both as a hospital-based programme and as an outpatient consultative service^22^ (integrated or separate) to other subspecialties of medicine such as haematology,^23^ nephrology^24^ and oncology,^25^ and in multimorbidity^26^ where evidence suggests that screening for frailty and delivering CGA-based care can improve treatment decision-making and reduce risk of institutionalisation when applied to other chronic conditions.^27 28^ Meta-analyses have demonstrated that CGA in older HIV-negative individuals can delay the development of disability, reduce admissions and hospital stays, and improve survival and functional ability.^27–29^ However, it is not clear whether CGA can improve outcomes for those OPWH with frailty.

There are few geriatric clinics for people with HIV with published data^11 30–32^; most are ageing clinics set up in Europe and the USA, with different objectives according to local circumstances which lack robust evaluation. Therefore, this will be the first study to evaluate the feasibility of screening for frailty and applying the CGA, delivered through a joint HIV-ageing clinic (the ‘Silver Clinic’) in outpatient HIV services. Our findings can inform the implementation of models of care for PLWH at risk of frailty.

### Objectives

The aim of this study is to assess the feasibility and acceptability of screening for frailty in OPWH and the Silver Clinic intervention, using a CGA approach; and to test the feasibility of a randomised controlled trial (RCT) to evaluate this intervention in the wider HIV setting. The main objectives are (1) to determine a sample size and primary outcome for a definitive RCT and (2) to explore what frailty means, what outcomes matter and the experience of the trial processes for OPWH, including communication about the trial, recruitment, randomisation, completion of measures and experience of participation in the trial. Secondary objectives are to (3) to undertake preliminary cost/service utilisation analysis and establish cost analysis outcomes for a definitive trial; (4) evaluate the feasibility and acceptability of implementing frailty screening and the Silver Clinic as part of HIV care; (5) to identify development needs and changes required to optimise the referral pathways, clinic structures and the intervention in preparation for a definitive trial and (6) to explore the acceptability of measures of frailty for OPWH. The objectives of the health economic analysis are: (1) to estimate the costs of the intervention; (2) to understand and estimate the costs of formal health and social care and informal care among patients with HIV and frailty and (3) to examine the feasibility of conducting cost-effectiveness analysis of this intervention in the full trial.

## Methods and analysis

### Trial design

The Silver Clinic feasibility study will use a mixed-method RCT design. Participants will be randomised 1:1 to two parallel groups: usual care or the Silver Clinic intervention, (including the CGA). Quantitative data (including process data and participant outcome measures at baseline, week 26 and week 52) will be collected alongside nested qualitative interview data from a subset of participants.

### Setting

Participants will be recruited from the HIV unit at the Royal Sussex County Hospital (RSCH), University Hospitals Sussex National Health Service (NHS) Foundation Trust (UHSx), Brighton, UK. The UHSx is an NHS foundation trust consisting of seven hospitals, providing both unscheduled and planned clinical services across Brighton and Hove and West Sussex. Data collection will take place at either the RSCH where participants receive their usual HIV care or at the Clinical Research Facility, RSCH.

### Eligibility criteria

Inclusion and exclusion criteria are shown in table 1.

**Table 1 T1:** Inclusion and exclusion criteria

Inclusion criteria	Exclusion criteria
PLWH aged 50 years or older with evidence of frailty scoring 3+ on frailty screening, using the FRAIL scale^33^	PLWH aged under 50 or not defined as frail
Consent to contact the GP	Attended the Silver Clinic during the last 12 months

GP, general practitioner; PLWH, people living with HIV.

### Patient and public involvement

A patient and public representative is a named coapplicant on this study (GP) and is the HIV representative of community works for all voluntary HIV organisations. Community works is the largest network of voluntary organisations in Sussex. They are also the manager of Lunch Positive, a weekly lunch club for PLWH providing a community space where OPWH in particular have the opportunity to socialise and access HIV peer support. They will chair the dissemination working group of patient and public involvement (PPI) and community representatives. Additional PPI representatives recruited during the trial will sit on the dissemination working group. They will be actively involved in the development of the study resources, impact and dissemination strategy and all associated activities. The group will have input on study design and recruitment strategies, review of participant facing materials, input into study conduct, monitoring, evaluation and dissemination of results to participants, service users, community and national HIV organisations.

### Trial procedures

The schedule of assessments is summarised in table 2.

**Table 2 T2:** Summary of trial procedures

Study visit day	Within 4 weeks Baseline	Day 0	Week 26 ±14days	Week 52 (12 months) ±14 days
Description of visit	Screening	Baseline	First follow-up	Final visit
Informed consent	X			
Review eligibility	X	X		
Demographic data*	X			
Antiretroviral/medical history	X	X	X	X
Healthcare utilisation data†		X	X	X
Silver Clinic consultation (intervention arm only)		X	X	X
Usual care (control arm)		X	X	X
Frailty measures‡		X	X	X
PRO§		X	X	X

*Comorbidities, time since HIV diagnosis, duration living with HIV, CD4, viral load, number of non-ART medications, number of falls in last 6 months.

†Number of referrals to primary, secondary and social care.

‡Fried frailty phenotype measure, FRAIL scale, Timed Up and Go test, Rockwood clinical frailty scale, Montreal Cognitive Assessment.

§Patient-reported outcomes (PRO) as HIV PROM, EuroQol, Adult Social Care Outcomes Toolkit, Client Service Receipt inventory, Consultation and Relational Empathy.

### Recruitment

Eighty-four participants will be recruited from the RSCH. Potentially eligible individuals will be identified at their routine HIV annual health check attending the Lawson Unit in Brighton. The HIV annual health check takes place for all service users as part of usual care. The health check is performed by nurses and includes assessment of weight, blood pressure, urinalysis, mental health assessment, sexual health screening, adherence review and cervical cytology and contraception. During this assessment, patients 50 years and over will be screened for frailty using the FRAIL scale.^33^ Those with evidence of frailty on their screening will then be informed of the study and if they express an interest in participating will then be put in contact with the research assistant or nurse to explain the full details of the study, answer any questions and to give informed consent (see online supplemental material). Participants will be consecutively enrolled during the period of recruitment. Recruitment commenced October 2021 and will continue until March 2023, the study is expected to be completed by October 2023.

10.1136/bmjopen-2022-070590.supp1Supplementary data

For those that decline to take part in the study they will be provided with an information leaflet about frailty and their physician will be informed about the frailty screening we have done as part of their HIV usual care. Their HIV clinician can refer them to the Silver Clinic as per normal pathways once the feasibility study is complete. These patients will also be asked whether they are happy to share their reasons for declining and if so their answers will be recorded.

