### Feasibility outcomes and progression criteria

#### Primary outcomes

To determine whether a definitive trial is feasible, we will examine the recruitment rates, completion rates of study outcome measures and retention at specific time points. A priori criteria for trial feasibility and progression to full trial without changes to the trial design are as follows (see table 3 for further details).

Recruitment of 60% of eligible patients.Recruitment of 84 patients within 6 months; from first patient randomised.Retention of 70 participants (allowing up to 15% attrition) to primary end point (6 months).Outcome measure completion for 90% of available participants at each time point.

**Table 3 T3:** Silver study feasibility outcomes, contributing data and progression criteria

Objective	Feasibility outcomes	Contributing data	Progression criteria Green	Amber	Red
1	Identification and recruitment of eligible patients*	Screening and recruitment log	≥60% eligible recruited	59%–40%	<40%
3	Retention of participants at follow-up*	Participation data	≥70 pts at 6 months ≥55 pts at 12 months	74%–60% 59%–40%	<60% <40%
4	Contamination of the control arm	CGA service data	≥10% participants receive a CGA within usual care	≥11%–20%	≥20%
5	Outcome measure completion*	Participation data	Missing data of ≤10% for each measure. Participant-reported acceptability.	11%–25% Some	>25% None
6	Participant satisfaction with care	Participant questionnaires and interviews	Reported as acceptable (or can be with minimal modification)	Reported as acceptable with modification	Intervention not acceptable

*Primary focus; Traffic-light progression criteria^50 51^—Green: likely no concerning issues, Amber: potentially remediable issues, Red: potentially intractable issues.

CGA, comprehensive geriatric assessment.

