#### Secondary outcomes

Health service utilisation (Client Service Receipt Inventory (CSRI)), social care (Adult Social Care Outcomes Toolkit, ASCOT) and physical and mental health components of the HIV PROM and EuroQol index score and visual analogue scale at 6 and 12 months. In addition, satisfaction with care will also be measured at each timepoint using the CARE measure.

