### Data collection

Baseline demographic data will be collected including personal characteristics (age, gender, sex at birth, ethnicity) and social factors (marital status, employment status, residential status, formal education level, annual income) and comorbidities. Demographic data and patient record data capture for the enrolment and follow-up forms will be done by manual data keying or electronically. Manual data keying is performed in a secure online browser-based platform called REDCap. Electronic data capture entails local extraction of data from clinical electronic databases and will be stored securely on the UHSx systems, HIV drive. Only the research team (including research administrator) will have access to these data and will not be made available outside the team or institution.

Process data will be collected to understand intervention delivery and trial design appropriateness. For the Silver Clinic intervention, records pertaining to CGA date, recommendations and follow-up will be collected. For trial process data, trial screening, recruitment rates, participation at each time point and amount of missing data will be recorded.

Standardised clinical outcome measures that represent multiple health and healthcare service domains will be collected at baseline, week 26 and week 52 postrandomisation. The positive outcomes HIV PROM measures multidimensional symptoms and concerns for PLWH^34 35^; the EuroQol EQ-5D-5L measures health-related quality of life^36^; the ASCOT measures social care-related quality of life^37^; the CSRI measures services and support accessed^38^; the Consultation and relational empathy measure (CARE) is used to assess interpersonal quality of healthcare encounters^39^; the Fried Frailty Phenotype and FRAIL scale are used to assess physical frailty^33 40^; and the Timed Up and Go test to assess functional mobility and falls risk.^41^ Physical tests will be conducted by the researcher and questionnaires will be completed with support of the researcher.

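### The stated recruitment and completion dates leave no time for the week-52 visit of participants randomised after about October to mid-November 2022, which puts the 12-month data and the 12-month retention criterion at risk

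*Protocol article*

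**What the plan says.** The Recruitment section gives the calendar: "Recruitment commenced October 2021 and will continue until March 2023, the study is expected to be completed by October 2023". Only months are given, and the shape of accrual is not described beyond enrolment being consecutive.

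The follow-up schedule is the same for everyone. Under Data collection, the outcome measures "will be collected at baseline, week 26 and week 52 postrandomisation". Table 2 (Trial procedures) labels the last column "Week 52 (12 months) ±14 days" and calls it the final visit. The Secondary outcomes include the "EuroQol index score and visual analogue scale at 6 and 12 months". Nothing in the article shortens follow-up for people who enter late.

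Table 3 has a retention row, starred as a primary focus, whose green cell reads "≥70 pts at 6 months ≥55 pts at 12 months". The list of a priori criteria above that table places the primary end point at 6 months and also asks for "Recruitment of 84 patients within 6 months; from first patient randomised".

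**The concern.** Between the end of recruitment and study completion there are roughly 26 to 35 weeks. That is enough for a 26-week visit but not for a 52-week visit. If the dates are followed as written, late recruits will be stopped by the calendar before their final assessment.

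The 12-month green criterion is a count of people, not a proportion of those who could have been seen. A participant cut off by the end date therefore lowers it exactly as a drop-out does. A signal meant to show whether participants stay in the trial would partly measure when the study closed. The 12-month outcomes and the week-52 service-use and cost data would also come from a smaller sample, made up of earlier recruits. That reduces what they can contribute to planning a definitive trial.

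**Working it through.** **Inputs.** Recruitment October 2021 to March 2023 and completion by October 2023 (Recruitment). Final visit at week 52 ± 14 days (Table 2), counted from randomisation (Data collection). Planned total 84 and attrition 15% (Sample size). Green at 12 months at least 55 (Table 3). Because only months are given, each date is varied from the first to the last day of its month.

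**The plan's own sample size.** 35 / (1 − 0.15) = 41.2, rounded up to 42 per arm, 84 in all. This reproduces.

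**Dates; no assumption about accrual is needed.**

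| Last randomisation | Week 26 (window) | Week 52 (window) |
|---|---|---|
| 1 March 2023 | 30 Aug 2023 (16 Aug to 13 Sep) | 28 Feb 2024 (14 Feb to 13 Mar) |
| 31 March 2023 | 29 Sep 2023 (15 Sep to 13 Oct) | 29 Mar 2024 (15 Mar to 12 Apr) |

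The most favourable combination is last randomisation on 1 March 2023, visit 14 days early and completion on 31 October 2023. Week 52 for the last recruit then falls on 14 February 2024, 106 days (about 3.5 months) after completion.

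The latest randomisation that can reach week 52 is the completion date minus 52 weeks, plus 14 days if the visit is made at the early edge of its window:

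- Completion 1 October 2023, visit on time: 2 October 2022.
- Completion 31 October 2023, visit 14 days early: 15 November 2022.

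**How many are affected, assuming even accrual.** Number able to reach week 52 = 84 × (days from start to cut-off) / (days from start to end of recruitment). Expected number seen = that × 0.85, taking the plan's 15% attrition to apply at 12 months as well (a second assumption). Retention needed for green = 55 / number able to reach week 52. The last column is the binomial probability of at least 55 at 85% retention.

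| Case | Able to reach week 52 | Expected seen | Retention needed | Chance of ≥55 |
|---|---|---|---|---|
| Least favourable: 31 Oct 2021 to 31 Mar 2023, cut-off 2 Oct 2022 | 84 × 336/516 = 54.7 | 46.5 | over 100% | under 0.1% |
| Central: 1 Oct 2021 to 31 Mar 2023, cut-off 15 Nov 2022 | 84 × 410/546 = 63.1 | 53.6 | 87% | 38% |
| Most favourable: 1 Oct 2021 to 1 Mar 2023, cut-off 15 Nov 2022 | 84 × 410/516 = 66.7 | 56.7 | 82% | 80% |
| All 84 followed to week 52 | 84 | 71.4 | 55/84 = 65.5% | over 99.9% |

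Sixteen combinations were run: first or last day of each of the three months, with and without the early edge of the window. The expected count is below 55 in 14 of them and above 55 in two.

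**The 6-month recruitment criterion.** If 84 were recruited within 6 months of a first randomisation in October 2021, the last week-52 window would close between 15 April and 15 May 2023, comfortably before October 2023. But that schedule contradicts the recruitment window of about 18 months.

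**The case against.** The best defence is that the damage is limited. The primary end point is at 6 months, and week 26 fits: on time it falls by 29 September 2023 even for the last possible recruit, and only the late edge of the window (13 October) could overrun a completion at the very start of October. The bulleted progression criteria contain no 12-month target; the figure of 55 appears only in Table 3. The completion date is given as an expectation, and a forecast is easily corrected. All of this stands and confines the point to the 12-month elements. It does not remove the conflict, because Table 3 stars the retention row as a primary focus and week 52 is the stated final visit.

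A reader might infer that green at 12 months will be missed. The documents do not support that. It needs even accrual and particular days within the months, and neither is stated. The most favourable reading gives an expected 57, and front-loaded accrual would ease the problem further, just as back-loaded accrual would worsen it. The consequence of falling short is also moderate. Expected counts of about 47 to 54 are 56% to 64% of 84, which lies in the amber band (59% to 40%) or in the gap between that band and 55/84. Red (below 40%) is not in prospect.

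A reader might also infer that the plan counts late recruits as lost to follow-up. It does not say so. The available-case rule under Analysis concerns the outcome comparisons and sets no retention denominator, and the promised flow chart could show administrative cut-off separately. A count threshold is nevertheless reduced by anyone not seen, whatever the reason. Nor does anything in the article suggest that late recruits differ from early ones, so the loss is chiefly one of numbers and interpretability. The interviews, at up to 15 per arm (30 in all), could be filled from the expected completers.

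Finally, the criterion of 84 within 6 months would make the calendar work. But the article states actual recruitment dates that contradict it, so it is a third statement to reconcile and not an answer.

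**Conclusion.** The point holds, limited to the 12-month elements. The recruitment window, the completion date and the week-52 final visit cannot all be met. This follows from date arithmetic alone, and the shortfall for the last recruit is at least about 3.5 months. Participants randomised after a date between 2 October and 15 November 2022 cannot reach week 52 by completion.

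The size of the effect on the count of 55 rests on two assumptions: even accrual, and 15% attrition carried through to 12 months. Under them about 55 to 67 of 84 could reach week 52, so about 17 to 29 could not, and about 47 to 57 would be seen. The 12-month green criterion is therefore at risk because of the calendar, but its failure is not established. The 6-month primary end point is not affected.

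**What to change.** Restate study completion as last randomisation + 52 weeks + 14 days. With recruitment to the end of March 2023 that is about mid-April 2024. In the same edit, reconcile the recruitment dates with the criterion of 84 recruited within 6 months. The cost is a timeline about six months longer, with no extra participants.

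If October 2023 must stand:

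- State the last randomisation date from which a week-52 visit is expected.
- Base 12-month retention and completion only on participants whose week-52 window closes before completion. For the whole window to fit, this means randomisation by completion − 52 weeks − 14 days: 18 September 2022 for completion on 1 October 2023, or 18 October 2022 for completion on 31 October 2023.
- Express the 12-month threshold as a percentage of that denominator (55/84 = 65%), so that it measures retention and not the closing date.

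This second option is not free. It gives a smaller 12-month sample and amends the follow-up schedule for late recruits. That amendment has to be reconciled with Table 2, with the Data collection section, and with the Usual care section, which ties control participants' offer of the Silver Clinic to the end of 12 months.
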